## **6. Information Provided to Participants and Informed Consent**

Participants will be asked to provide consent to anonymous screening. If participants appear to be eligible, they will consent to enter the study by completing [Error! Reference source not found.](#) and provide their full contact details. Participants must complete this form before the assessment phone call and any other study-specific procedures can commence.

The ePIS presented to participants will contain no less detail than: what it will involve for the participant; the implications and constraints of the protocol; and the known side effects and any risks involved in taking part. Further, it will be clearly stated that participants are free to withdraw from the study at any time, for any reason, and with no obligation to give the reason for their withdrawal. Potential participants will be allowed as much time as they wish to consider the information in the ePIS and eICF, and the opportunity to question the research team, or other independent parties to decide whether they will participate in the study. A copy of the signed eICF will be created on the study database platform, accessible only to the research team.

## Section G. Research Procedures

### 1. Baseline Assessments and Procedures

If a person is eligible after full assessment, the researcher will send the potential participant a link by email or text to complete the baseline assessment online. The questionnaires and learning task will take about 1 hour. Participants will be asked to complete an online survey capturing socio-demographic information, medical history, questionnaires and tasks regarding mental health and associated quality of life and work (**Table**) (Error! Reference source not found. **BASELINE ASSESSMENT**), weigh themselves (we will provide a scale if participants do not have one), and provide saliva the first hour of the morning that is convenient to them, and a stool sample. We will collect data which are shown in **Table**, below:

**Table 2: Self-reported data collection at baseline**

|    |                                           |                                                                                                                                                                                                                                                                                                                                                                                                                                                                                                                                                                                                                                                                                                                                                         |
|----|-------------------------------------------|---------------------------------------------------------------------------------------------------------------------------------------------------------------------------------------------------------------------------------------------------------------------------------------------------------------------------------------------------------------------------------------------------------------------------------------------------------------------------------------------------------------------------------------------------------------------------------------------------------------------------------------------------------------------------------------------------------------------------------------------------------|
| 1. | Contact details                           | Name and address, telephone numbers, email address.
Name and address and contact details of participant's GP                                                                                                                                                                                                                                                                                                                                                                                                                                                                                                                                                                                                                                         |
| 2. | Demographic and clinical information      | Postcode, sex, age, marital status, level of education, ethnicity, number of episodes of depression, age of onset of first depression episode, current antidepressant treatment (type/dose), current psychological therapy for depression, and current medical conditions                                                                                                                                                                                                                                                                                                                                                                                                                                                                               |
| 3. | Self-rated questionnaires and assessments | Patient Health Questionnaire-9 (PHQ-9); Snaith-Hamilton Pleasure Scale (SHAPS); General Anxiety Disorder Scale (GAD-7); Perceived Deficits Questionnaire-5-item (PDQ-5); Work and Social Adjustment Scale (WSAS); Short-Form 12 Health Survey (SF-12); Probabilistic instrumental learning task (PILT)                                                                                                                                                                                                                                                                                                                                                                                                                                                  |
| 4. | Self-reported anthropometric measures     | Weight, height                                                                                                                                                                                                                                                                                                                                                                                                                                                                                                                                                                                                                                                                                                                                          |
| 5. | Saliva/stool samples                      | We will send participants a sample kit for collecting salivary cortisol and stool samples. Collection and packaging the stool sample will take less than 5 minutes plus time taken to post the sample in the pre-packaged and paid for posting pack. Salivary samples are taken in the first hour of the designated day and take about 2 minutes to collect and deal with each sample, which is collected by putting a dental roll in the mouth and extruding it into a plastic container. Participants will be able to do other things during collection but not eat. Samples will be collected on waking, and at 30, 45, and 60 minutes after waking. The samples will be sent back to the laboratory in a pre-addressed and stamped padded envelope. |

Note: Postcode will be converted to an index of multiple deprivation score and the demographic variables will be presented by group at baseline for descriptive purposes only.

After all baseline assessments are complete, participants will be allocated by minimisation 1:1 to the KD group or control group. A researcher will embed a non-deterministic algorithm in the Redcap database. This algorithm aims to produce treatment groups balanced for important prognostic factors by minimising on the following variables (as below). Only after eligibility and consent is confirmed will the database reveal the allocation. Investigators delivering the intervention will not be blinded, but the outcome is collected blind (by self-report), and those involved in analysing the outcome data will be blinded to allocation.

- BMI (less than 30 kg/m^2 vs. 30+ kg/m^2)
- Depression severity (PHQ-9 score: 15-19 [moderately severe] vs. 20-27 [severe])

All follow-up is done online and without trial staff and will therefore not be subject to observation bias. Following randomisation, participants will be given information and advice for their respective group.

The questionnaire with details is described in **APPENDIX 6. BASELINE ASSESSMENT** and **APPENDIX 8. SELF-REPORTED QUESTIONNAIRES**. The probabilistic instrumental learning task consists of two pairs of symbols with one pair associated with win outcomes (win £1 or no change) and the other associated with loss outcomes (lose £1 or no change). Each symbol in the pair corresponds to reciprocal probabilities (0.7 or 0.3) of the associated outcomes occurring. Participants are required to choose between the two symbols in order to maximize their winnings. Once a choice is made, outcome feedback is provided. In order to maximize their winnings, participants use the outcome feedback to gradually learn the symbol–outcome associations over time, such that they consistently choose the symbol associated with high-probability win and avoid the symbol associated with high-probability loss. Note that different symbols are used at each visit to minimize learning effects confounding subsequent performance. Further details for this task are provided in this paper.

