## 2. Subsequent Visits

Follow-ups will be online only. Participants in both groups will be asked to complete questionnaires and tasks regarding mental health and quality of life and work (**Table 3**). Participants will be asked to weigh themselves, provide saliva (in the morning) and stool samples as outlined above. Two-week and 4-week assessments should take about 5 minutes to complete and the 6-week and 12-week assessment about 30 minutes. In the unlikely event that there are participants that default from completing the online questionnaires and have not contacted us, a researcher will make two attempts within 3-days to phone the participant directly to administer the PHQ-9 (primary outcome) over the phone.

We will invite about 20 participants to a Teams call one-to-one interview to discuss their experiences of trying to follow the diet assigned to them, the support on offer, and the perceived effects of it on their wellbeing. We will select participants to achieve a range based on their adherence to the diet and their response as measured by change in PHQ-9. We will analyse these interviews using simple content analysis. We anticipate interviews lasting up to 30 minutes. We will audio record them prior to analysis then destroy the recordings once the analysis is complete and we are confident of the meaning. The interviews will be audio only because both participants will turn off their video function. This will allow us to use the automatic transcription in Teams to enable us to use anonymised quotes in the write-up.

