## 7. Please detail all expenses or gifts that will be offered to participants.

All participants will be reimbursed for their time and effort after each fully completed assessment after baseline (vouchers = £10 at week 2 and week 4; £30 at week 6; £30 at week 12; £10 qualitative interview after week 12). A pro-rated £10 gift voucher will be offered to the participant for partial completion where PHQ-9 (primary outcome) is the only measurement administered over the phone. Participants randomised to the control group will receive £20 shopping vouchers every two weeks to purchase vegetables and fat replacement. Participants in the ketogenic diet group will receive food to support dietary adherence.

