**2. Will the research involve deliberate deception of participants?**

Yes ☐

No ☒

If **yes**, justify why deception is used, describe deception and debriefing process, and include debriefing documents in the application

The aim of the study will be described accurately, but in broad terms, rather than specific detail. The PIS will describe the aim to assess the impact of a dietary intervention, without specifically mentioning ketogenic diet, as this could influence participants' dietary behaviours such that participants in the control arm choose to follow this diet, which will contaminate the study and could make the results difficult to interpret and undermine its purpose. Once randomisation has occurred, the participant will receive educational materials and consultation with a registered dietitian about the specific dietary intervention. At the end of the study, we will write to all participants to share the hypothesis and provide the results (**APPENDIX 12. Final letter for participants**).

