#### *Study steering committee*

The committee will consist of clinicians with relevant clinical expertise and experience in clinical trials. They will not be members of the University of Oxford and not related to the investigators. According to NIHR's Research Governance guidelines, the SSC will examine the protocol and give advice on the conduct of the study and take on the roles of the DMEC with respect of monitoring safety if this is required. This is an open-label trial where the interventions are dietary and not known to cause harm and there are no early stopping rules that would require this. The SSC will receive and review information on the progress and accruing data of the trial and will provide advice on the conduct of the study to the investigators.

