| 1. Replace “registered dietitian” with “supervised by a dietitian”                                                                                                                             | 
There are three reasons for this change: first, we are short of registered dietitians to deliver support calls, so our registered dietitians will arrange training for new researchers. These researchers will initially deliver the calls under the supervision of our registered dietitians to ensure quality. They will conduct the calls independently but will seek advice from registered dietitians as needed.
 
Second, our support calls do not involve extensive nutritional advice, and our dietitians have collected and prepared common questions with correct answers, so this change will not affect the integrity of the intervention.
 
Third, this change is safe for our participants because patients with special dietary requirements or bowel issues were not included in this study.
 |
| 2. We have revised “APPENDIX 16. Qualitative interview questions” to use more conversational language and added further questions about patients' experiences and attitudes towards the meals. | This change helps researchers follow the process more easily, facilitates our conversations with participants, and increases our understanding of how patients feel about the entire study.                                                                                                                                                                                                                                                                                                                                                                                                                                                                                                                                                                                                                                   |

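### The protocol calls PHQ-9 collection blind and free of observation bias, but participants know their diet and a researcher phones non-responders for the primary outcome

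*Combined protocol and SAP*

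**What the plan says.** Protocol Section G.1, in the text on minimisation after Table 2, makes two claims about outcome collection. The first is about blinding: "Investigators delivering the intervention will not be blinded, but the outcome is collected blind (by self-report"). The second is about staff influence: "All follow-up is done online and without trial staff and will therefore not be subject to observation bias".

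Section G.2 begins in line with this ("Follow-ups will be online only"), then provides a fallback for people who default: "a researcher will make two attempts within 3-days to phone the participant directly to administer the PHQ-9 (primary outcome) over the phone". The protocol describes this as unlikely to be needed. Section G.7 sets a reduced £10 voucher for "partial completion where PHQ-9 (primary outcome) is the only measurement administered over the phone", so the phone route is a planned mode of collection.

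On what participants know, the answer on deception in Section I (Ethical considerations) says: "Once randomisation has occurred, the participant will receive educational materials and consultation with a registered dietitian about the specific dietary intervention". Section L, under the steering committee, says: "This is an open-label trial where the interventions are dietary and not known to cause harm".

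The SAP does not distinguish scores by mode of collection. The primary model in SAP 4.1 contains group, time, their interaction, the minimisation variables and a subject effect. SAP 4.5 varies the assumptions about missing data, and SAP 4.6 sets outliers to missing.

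**The concern.** The second claim in G.1 is an inference: no staff are involved, so there is no observation bias. G.2 removes the premise for part of the primary-outcome data, so the conclusion does not follow for those scores. Phone scores come only from people who did not respond online, and that group may differ in size between arms. If the caller knows the allocation, or if people answer differently by voice than on a screen, the effect enters the primary contrast and no planned analysis would show it.

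The statement that collection is blind fails for a different reason. With a self-reported scale the participant is the assessor, and from randomisation the participant knows which diet they have been given. Self-report removes the staff rater but does not mask the rater who remains.

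What is at stake is mainly what may be concluded. If the G.1 wording is carried into the report, readers would be told that the primary outcome has a protection the design does not provide.

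**Working it through.** **1. The statements side by side**

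| Property claimed in G.1 | What other sections say |
|---|---|
| All follow-up is online | G.2: PHQ-9 by phone for those who default; G.7: voucher rate for that case |
| No trial staff involved | G.2: a researcher administers the PHQ-9 |
| Hence no observation bias | Premise false for phone-collected scores; no visible text requires the caller to be masked, scripted or separate from diet support |
| Outcome collected blind | Section I: participants are told their specific diet; Section L: open-label |

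**2. What masking does exist.** The information sheet does not name the ketogenic diet (Section I). The control diet is meant to be a credible dietary treatment (Section E). People who have read the protocol or registration are excluded (Section F.3). Together these support masking to the hypothesis, not to treatment.

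**3. The plan's own figure.** Inputs from SAP 2.2 and 4.1: difference 5, SD 6, two-sided 5%, power 90%.
- Normal approximation: n per arm = 2 × (1.960 + 1.282)² × 6² / 5² = 30.3, so 31.
- t-test version: 31.25, so 32 per arm and 64 in total, as stated.
- Attrition: 64 / 0.65 = 98.5, so 99, stated as 100.

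The plan's figure is reproduced, and this point does not challenge it.

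**4. Size of the phone-route bias.** The documents give neither the phone rate nor the size of a caller or mode effect. The values here are assumptions.
- Phone completion in one arm only, 15% of its week-6 scores, shifted by 2 to 3 points: 0.15 × 2 = 0.30; 0.15 × 3 = 0.45.
- Phone completion in both arms, rates differing by 10 percentage points, same shift: 0.10 × 2 = 0.20; 0.10 × 3 = 0.30.

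The range is 0.20 to 0.45 points, or 4% to 9% of the 5-point target (0.20/5; 0.45/5).

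**5. Effect on type I error.** For bias B and N analysed in equal arms, SE = 6 × √(4/N): 1.50 for N = 64 and 1.279 for N = 88, the number randomised. The two-sided error is 1 − Φ(1.96 − B/SE) + Φ(−1.96 − B/SE).

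| Bias B (points) | N = 64 | N = 88 |
|---|---|---|
| 0.20 | 5.2% | 5.3% |
| 0.30 | 5.5% | 5.6% |
| 0.45 | 6.0% | 6.4% |

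Example: B = 0.45, N = 64 gives B/SE = 0.30, and 0.0485 + 0.0119 = 0.0604.

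As an outer bound, suppose 35% of scores came by phone (borrowing the plan's attrition allowance) and the caller shifted the arm difference among them by 3 points. Then B = 0.35 × 3 = 1.05, and the error is 10.8% (N = 64) or 13.0% (N = 88). Nothing in the documents suggests that phone use was that high.

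**6. Size of a self-report bias.** A reporting shift from knowing the diet could affect every score, so no phone share dilutes it. An assumed shift of 1 point in the arm difference gives 10.2% (N = 64) or 12.2% (N = 88); 2 points gives 26.6% or 34.6%. These figures show scale only and do not predict a bias of that size.

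**The case against.** The strongest reply is that G.1 speaks of staff-observer influence, which online self-completion largely removes, and that the trial is openly called open-label elsewhere. The word blind may be meant as masking to the hypothesis; the exclusion of people who have read the protocol uses the term in that sense. This stands as an explanation of intent, and the safeguards in Sections E, F.3 and I deserve credit. It does not rescue the wording, because the stated reason for blindness is self-report and the stated reason for no observation bias is the absence of staff.

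A reader might infer that the people coaching participants on diet also score them by phone. The documents do not show this. The amendment says of trained researchers "These researchers will initially deliver the calls under the supervision of our registered dietitians to ensure quality", but those are support calls, and no text says who makes the PHQ-9 calls. Likewise, a reader might conclude that callers are unmasked. That is an argument from silence: the appendix contents are not visible, and SAP 2.3 sends further detail on allocation concealment to a published protocol outside these documents. What can be said is that masking and separation of the caller are not required in the text available.

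The phone route is described as unlikely, its rate is unknown, and the bias above is small. Setting phone scores to missing discards observed outcomes from people prone to non-response, which is a fair objection to making it the main analysis but not to a supportive one. Finally, SAP 2.2 reports that recruitment stopped at 88, so changes to how calls are made may come too late.

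**Conclusion.** The point holds as an error of description with a modest analytic consequence. G.1 attributes to the primary outcome a blindness and a freedom from observation bias that G.2, G.7, Section I and Section L contradict. The phone-route bias is probably small: 0.20 to 0.45 points and type I error of about 5.2–6.4%, resting on assumed phone rates, an assumed 2–3 point effect, SD 6, and 64 or 88 analysed. The broader exposure is self-report by participants who know their diet. Hypothesis masking and a credible control may reduce it, but no analysis can remove it.

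A reader might go further and infer that the primary result is materially biased, or that the final report will claim bias is absent by design. The documents support neither: no phone rate or bias is documented, and the protocol itself calls the trial open-label. The wording should be corrected and the extent of phone collection made visible.

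**What to change.** 1. **Wording.** Reconcile G.1 with G.2. Replace the blind-collection and no-observation-bias statements with: *open-label; participant-reported; participants aware of their diet but not told the hypothesis; staff administer the PHQ-9 by phone to non-responders*. Carry this into the conclusions of the report.
2. **Remaining calls.** Have any phone PHQ-9 still to be done read verbatim by an existing team member who gives no diet support and cannot see allocation.
3. **Counts.** Report the number of phone-collected PHQ-9 scores by arm and time point. These cases can probably be recovered from existing records. At weeks 6 and 12 full completion earns £30 and phone-only £10. At weeks 2 and 4 both amounts are £10, but a PHQ-9 without its companion GAD-7 would point to a phone score.
4. **Analysis.** Add one supportive sensitivity analysis to SAP 4.5: the primary model refitted with phone-collected scores set to missing. The existing available-case mixed model handles this directly. The primary analysis stays as planned, so its power is unaffected.

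The cost is a few sentences, a rota rule among existing staff, one table and one model run. The one drawback is more missing data in the added analysis. If follow-up is already complete, items 1, 3 and 4 still apply.
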